##### Cognitive reserve

We will evaluate cognitive reserve using the Cognitive Reserve Index questionnaire (CRIq) [41]. The CRIq is a valid and reliable half-structured interview, which quantifies cognitive reserve over an individual’s lifetime using three established measures of cognitive reserve: education (CRI-Education), occupation (CRI-WorkingActivity), and engagement in cognitively stimulating activities (CRI-LeisureTime) [42]. The three sub-scores can be combined into an overall score (CRI-Index). All measures are age-adjusted to allow for comparisons between different age groups.

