### Sample size

Sample size calculation was based on the main (first) research question for the two primary outcomes, the STROOP and the WAFG, and was conducted using G*Power (version 3.1.9.2). The alpha level was set to α = .05 with the power to detect significant differences of 0.8. A total of *N* = 42 participants will be needed to detect a medium effect size of *d* = 0.25 [24, 26, 62] between pre- and post-assessment, assuming a correlation between repeated measures of *r* = .5. We will adjust for multiple comparisons using the Bonferroni correction. A total sample size of *N* = 60, with *n* = 30 individuals per group, will be required to account for a 30% drop-out rate [24].

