### Statistical analysis

Statistical analysis will be conducted using IBM SPSS Statistics 26 (IBM Corporation: Armonk, NY, USA). We will use the intention-to-treat dataset, considering all participants as randomised who have completed at least pre-assessment and regardless of adherence to protocol. Hypotheses will be tested two-sided on an alpha level of α ≤ .05, which will be adjusted for multiplicity for primary outcomes by applying the Bonferroni correction. Multiple imputation techniques will be applied to account for missing data assuming that data are missing at random (MAR). Additionally, we will report reasons for withdrawal and analyse them qualitatively.

Primary and secondary outcomes will be analysed using 2 (group) × 3 (time) repeated measures analysis of variance (ANOVAs) with group as between-subjects factor and time-point of assessment (pre-, post-, 3-month follow-up) as within-subjects factor. Bonferroni’s post hoc test will be conducted to test hypotheses. We predict a significant group x time interaction, in which the LLG will outperform the WLCG at post- compared to pre-assessment (hypothesis 1) and at 3-month follow-up compared to pre-assessment (hypothesis 2). Partial eta square (*η*_*p*_^2^) will be used as an indicator of effect size.

For the LLG, exploratory subgroup analyses will be performed to evaluate whether effects of foreign language learning on cognitive outcomes are dependent on different levels of cognitive reserve (hypothesis 3) and foreign language knowledge and usage (hypothesis 4). Therefore, we will conduct multiple and simple regression analyses, respectively. The difference in primary outcome measures between pre- and post-assessment will be defined as the dependent variable. Age and indicators of cognitive reserve (CRI-Education, CRI-WorkingActivity, CRI-LeisureTime, and CRI-Index) (hypothesis 3) and the LSBQ-score (hypothesis 4) will be considered as independent variables.

Additionally, we will investigate whether short-term effects of foreign language learning on cognitive measures also apply to the WLCG after completing the control group programme. For this purpose, the WLCG will serve as its control. Using *t*-tests for dependent means, we predict a significant difference between the difference scores from 3- to 4-month follow-up compared to the difference scores from pre- to post-assessment.

To assess the robustness of results, we will perform sensitivity analyses for the following:

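### The exploratory hypothesis 3 regression lists CRI-Index alongside the three sub-scores that form it, so the individual CRI coefficients would be arbitrary or very unstable

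*Protocol article*

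**What the plan says.** The Aims section states hypothesis 3 as the expectation that the degree of cognitive reserve predicts change in cognitive scores. The Statistical analysis section places its test in one study arm and labels it exploratory: "For the LLG, exploratory subgroup analyses will be performed".

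For hypotheses 3 and 4 in that order, the method is: "Therefore, we will conduct multiple and simple regression analyses, respectively". The outcome is a change score: "The difference in primary outcome measures between pre- and post-assessment will be defined as the dependent variable".

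The predictors for hypothesis 3 are given as one list: "Age and indicators of cognitive reserve (CRI-Education, CRI-WorkingActivity, CRI-LeisureTime, and CRI-Index) (hypothesis 3"). For hypothesis 4 the only predictor is the LSBQ score.

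The Cognitive reserve section explains how the four CRI scores relate: "The three sub-scores can be combined into an overall score (CRI-Index"). It adds: "All measures are age-adjusted to allow for comparisons between different age groups".

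The article does not give the combination formula. It does not say that CRI-Index and the sub-scores go into different models.

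**The concern.** The plain reading is a single multiple regression with five predictors, one of which is built from three of the others. Such a model asks what total reserve adds once every component of it is held constant. If the total is a linear function of its parts, that question has no answer. If it is nearly so, the answer rests on whatever small residue is left, such as rounding.

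The interpretation of the four CRI coefficients is at stake. A reader of the results would want to know whether education, occupation, leisure activity or overall reserve goes with change. Under the listed model, the sign and p-value of each could depend on which term the software dropped or on rounding error.

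**Working it through.** **Inputs.** The five predictors, the regression type and the arm come from Statistical analysis; the Index as a combination, and the age adjustment, from Cognitive reserve. The group size of 30 comes from Sample size: "individuals per group, will be required to account for a 30% drop-out rate [24". A 30% loss would leave 30 × 0.7 = 21. The following are assumed, because the article does not give them: sub-scores and Index on a scale with SD 15, sub-score correlations of 0, 0.3 or 0.6, and the form of the combination.

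**The plan's own figure.** No number is stated for this regression. The nearby sample size is not in dispute. With effect size 0.25 read as Cohen's f, two time points, r = .5 and alpha .05/2, λ = f²·N·m/(1 − r) = 0.0625 × 42 × 2 / 0.5 = 10.5. Power at N = 42 is then .815, and 42/0.7 = 60, or 30 per group.

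**Case 1: exact linear combination.** Write Index = a + b₁·Edu + b₂·Work + b₃·Leisure. For any constant c, adding c to the Index coefficient, subtracting c·b₁, c·b₂ and c·b₃ from the sub-score coefficients and subtracting c·a from the intercept leaves every fitted value unchanged. The data therefore cannot choose among infinitely many sets of CRI coefficients. In 500 simulated data sets per scenario, the matrix (intercept, age, three sub-scores, Index; 6 columns) had rank 5 in every scenario, at n = 30 and n = 21. Age does not help: a further linear age adjustment of the Index would still lie in the span of the columns.

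**Case 2: a small residue remains.** VIF = 1/(1 − R²), where R² comes from regressing the Index on the other four predictors. In a sample of n, the expected size is roughly the population VIF × (n − 1)/(n − 5).

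- *Sub-scores explain 95% of the Index variance.* The population VIF is 1/0.05 = 20. At n = 30: 20 × 29/25 = 23.2. At n = 21: 20 × 20/16 = 25.0. Simulated medians were about 23 to 26.
- *Only rounding to whole numbers separates them.* Rounding variance is 1/12, so the population VIF is about 225/(1/12) = 2700. At n = 30: 2700 × 29/25 = 3132. At n = 21: 2700 × 20/16 = 3375. Simulated medians were about 3080 to 3370.

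Simulated median VIFs across both sample sizes and all three correlations:

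| Model | CRI-Index | Sub-scores | Age |
|---|---|---|---|
| As listed, exact combination | cannot be fitted | cannot be fitted | – |
| As listed, rounding only | 3080–3370 | 470–1160 | 1.1–1.2 |
| As listed, 95% explained | 23–26 | 5–10 | 1.1–1.2 |
| Age + three sub-scores | – | 1.1–2.2 | 1.1–1.2 |

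**What survives.** In case 1, the fitted values, R-squared and the joint test of the CRI scores are the same whichever redundant CRI term is dropped. The age VIF stays near 1 wherever the model can be fitted. The damage is confined to the separate CRI coefficients.

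**The case against.** The strongest reply is that the authors may intend separate models. The text speaks of analyses in the plural, says only that the scores will be considered as independent variables, and presents the Index as an optional summary of the sub-scores. How predictors are divided among exploratory models is also often left to an analysis plan. This reading is possible, but the article does not state it. The plural is already explained by two hypotheses and two primary outcomes, and all five predictors appear in one list under one method. If separate models are meant, the same short clarification is needed.

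Some stronger readings are tempting and do not hold:

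- *A reader might infer that hypothesis 3 cannot be answered at all.* It asks whether the degree of reserve predicts change, and the joint test of the CRI scores still addresses that.
- *A reader might infer that the standard errors would be wrong.* They would be correct for the fitted model, but very large.
- *A reader might infer that only 21 people are available.* The main analysis uses everyone with a pre-assessment, with multiple imputation. Twenty-one applies only to complete cases at the full assumed drop-out.

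It is also fair to say that the analysis is exploratory and that the redundancy would show as soon as the model was run.

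**Conclusion.** The point stands as a faulty stated predictor set, with modest severity. As listed, the hypothesis 3 model is rank deficient (5 of 6) if CRI-Index is a linear combination of its sub-scores. Otherwise it is nearly so, with a VIF for CRI-Index from about 23 to over 3000. The direction of this conclusion rests only on the article's statement that the Index combines the sub-scores. The size rests on assumptions about scale, rounding and explained variance, so no single figure in that range should be quoted as the expected one.

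The individual CRI coefficients, with their signs and p-values, would not be interpretable. No randomised comparison, primary or secondary result, alpha allocation or sample size depends on this analysis.

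**What to change.** Replace the single predictor list for hypothesis 3 with two separate models for each primary outcome: (a) age and CRI-Index; (b) age and the three sub-scores, without CRI-Index. State in advance which of the two is the main test of hypothesis 3 and treat the other as supportive. Model (b) has full rank and VIFs of about 1.1 to 2.2 under the same assumptions; model (a) contains no component of the Index and so avoids the dependence.

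The cost is one sentence in the Statistical analysis section. It needs no new data and no change to recruitment or assessments. The Trial status section reports recruitment still open with 54 enrolled at submission, so the wording could be settled before analysis.

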**Fig. 3 Fig3:**
[figure not shown]
CONSORT flow diagram of participants

The face-to-face screening will take around 2 h and will evaluate the remaining exclusion criteria. The CFD will be applied to exclude participants with suspected cognitive decline and the whispered voice test [37] will be used to ascertain sufficient hearing. Participants who indicated in the telephone screening to already have slight experiences in Spanish will take a placement test [61] to ensure that their previous skills are low enough (< level A1.1) for a Spanish course for beginners. Additionally, further baseline data will be collected (see section ‘Baseline variables’).

Subjects that meet eligibility criteria after the face-to-face screening will be randomly assigned to either the LLG or the WLCG. Within 2 weeks before the start of the language course or the three-week waiting period, both groups will participate in a pre-assessment. Both post- and 3-month follow-up assessments will be carried out within 2 weeks immediately (post) and 3 months (3-month follow-up) after the end of the intervention or the waiting period. After this, the LLG will have completed study participation while the WLCG will attend the control group programme consisting of the language course and a voluntary 4-month follow-up assessment.

Pre-, post-, and follow-up assessments will last around 2 h each and will be scheduled at the same time of day, either in the morning or in the afternoon, to control for day-dependent variability in cognitive performance. Assessments will include both the primary and secondary outcome measures listed in Fig. 1. The test order will be randomised by a computer for each individual. However, the WAFA, as the most straightforward task, will always be applied first to allow participants to become familiar with the computerised test system.

To enhance participant retention, we will arrange appointments for pre-, post-, and follow-up assessments with each participant individually before the start of the study. A confirmation document with the scheduled dates and times will be sent to participants. Additionally, participants will receive reminder phone calls 1 week before each assessment. There will be no financial compensation apart from the language course, which will be offered for free. However, participants may obtain information about their results and the conclusion of the study after having completed participation.

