We will examine the influence of protocol non-adherence by comparing the intention-to-treat to the per-protocol dataset. Participants will be included in the per-protocol dataset if they have completed at least pre- and post-assessment and a minimum of 14 h of formal language instruction (> 62% of the total course duration) referring to Bak et al. [26].Effects of missing values will be assessed by comparing results from the complete case (only including subjects without any missing values) to the imputed dataset.

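### Comparing complete cases with MAR-imputed data cannot test departures from MAR, so agreement between the two would not show robustness to drop-out tied to unseen scores

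*Protocol article*

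**What the plan says.** The Statistical analysis section of the protocol article sets the main approach: "Multiple imputation techniques will be applied to account for missing data assuming that data are missing at random". It then lists sensitivity analyses meant to show how robust the results are. The one for missing data reads: "Effects of missing values will be assessed by comparing results from the complete case", meaning participants with no value missing, against the imputed data.

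Two other provisions come near the subject. One concerns adherence: "We will examine the influence of protocol non-adherence by comparing the intention-to-treat to the per-protocol dataset". The per-protocol set itself requires a post-assessment, so it does not address people who were lost. The other is descriptive: "Additionally, we will report reasons for withdrawal and analyse them qualitatively".

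The Sample size section inflates the sample "to account for a 30% drop-out rate". No analysis in the document relaxes MAR.

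**The concern.** A sensitivity analysis should vary the assumption on which the main result depends. Here the main result depends on MAR: given arm and observed scores, people who left would have scored like those who stayed. The complete-case analysis rests on an equal or stronger assumption. If LLG members leave for reasons tied to a post or 3-month score that nobody saw, both analyses can be biased in the same direction and still agree.

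The comparison is listed under robustness, so agreement would naturally be read as reassurance. With the plan's own allowance for loss and unblinded participants, that reassurance could be wrong for the group-by-time contrast behind hypotheses 1 and 2.

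**Working it through.** **1. The plan's drop-out figure.** Inputs from the Sample size section: effect size 0.25, correlation 0.5, power 0.8, alpha 0.05 with Bonferroni over two primary outcomes (0.025 each), pre and post measurements. For the within-between interaction:

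- λ = f²·N·m/(1−ρ) = 0.25² × 42 × 2 / 0.5 = 10.5, with df 1 and 40.
- Power at alpha 0.025 is 0.815, so N = 42 reproduces (reading 0.25 as Cohen's f).
- 42/(1 − 0.30) = 60, and 0.30 × 60 = 18. The plan thus allows for 18 lost participants.

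**2. What the planned comparison measures.** Within one arm, let π be the fraction missing, C_o the mean change of those observed, C_m the true mean change of those missing, and C_mar the mean change that MAR imputation gives them.

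- Truth: (1−π)C_o + πC_m
- Imputed: (1−π)C_o + πC_mar, so bias = π(C_mar − C_m)
- Complete case: C_o, so bias = π(C_o − C_mar) + π(C_mar − C_m)
- Complete case minus imputed: π(C_o − C_mar)

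The gap that the plan inspects does not contain C_m. It shows how far leavers differ from stayers on observed scores. The term that measures departure from MAR is common to both analyses and cancels.

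**3. Illustration with two time points.** Assumed: 30 per arm, SD 1, correlation 0.5, higher scores better (for the two reaction-time primaries the sign reverses), 30% random loss in the waiting list control group (WLCG), 20 imputations from arm and pre score, Rubin's rules, test of change at 0.025, 3,000 runs. Overall loss is 30–31%. LLG loss follows a logistic model with intercept −1.1 and slope −1.5 on the named quantity. True effect 0:

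| LLG loss driven by | Complete case | Imputed | Mean absolute gap, one trial | Type I error (complete case / imputed) | Same verdict |
|---|---|---|---|---|---|
| Nothing (MCAR, 30%) | 0.002 | 0.002 | 0.074 | 0.022 / 0.018 | 98.8% |
| (a) Unseen post score given pre | 0.292 | 0.294 | 0.078 | 0.086 / 0.087 | 96.0% |
| (b) Unseen change | 0.335 | 0.258 | 0.096 | 0.125 / 0.075 | 93.6% |

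With a true effect of 0.5, (a) gave 0.801 in both analyses and (b) gave 0.836 and 0.754. In (a) the single-trial gap is about what harmless loss produces. In (b) it is only slightly larger.

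Further runs (1,500 each, true effect 0):

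- LLG loss driven by the raw unseen post score: 0.171 complete case, 0.262 imputed.
- LLG loss driven by the observed pre score: −0.166 and 0.005. The comparison does separate the two.
- Loss driven by unseen change in the same way in both arms: 0.005 and 0.005. The bias cancels in the contrast.

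**4. Illustration with three time points.** 30 per arm, true 3-month effect 0.35, LLG loss about 40%:

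- Driven by the unseen 3-month score: complete case 0.55, imputed 0.65 to 0.68. The excess is 0.55 − 0.35 = 0.20 and 0.30 to 0.33.
- Driven by the observed pre-to-post gain: 0.55 and 0.35. Imputation using the post score is unbiased, and the comparison shows the gap.
- Dependent on arm only: 0.36 and 0.36.

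**The case against.** Several points on the other side stand.

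- **Observed-score loss.** A reader might infer that the check misses all outcome-related drop-out. It does not. An LLG member who shows no gain at post and then skips the 3-month visit is missing at random given the post score; imputation handles that, and the complete-case result diverges. In one trial the divergence is noisy, however: a run with about 31% LLG and 10% WLCG loss gave 0.52 against 0.35, with a single-trial SD of the gap of 0.13.
- **Incentives.** The Participant timeline says: "After this, the LLG will have completed study participation while the WLCG will attend the control group programme". A reader might infer that the WLCG, still waiting for its course, will stay while the LLG leaves, and that this biases the result. Loss that depends on arm alone is MAR given arm and biased neither analysis. The same section also gives LLG members reasons to return: feedback on their results, pre-arranged appointments and reminder calls.
- **Equal bias and a fixed size.** A reader might infer that both analyses are always wrong by the same amount, or by a set percentage. Rows (a) and (b) show that equality is one case among several. If one assumes that LLG completers gain 0.50, that the 30% who leave gain nothing and that the WLCG does not change, the truth is 0.7 × 0.50 = 0.35 and the overstatement is 0.50/0.35 = 1.43. That 43% is the assumption restated, and no document supports it.
- **Withdrawal reasons.** The qualitative review helps to judge whether MAR is plausible. It does not put a size on the bias.
- **Unseen analysis plan.** Details of sensitivity analysis are often left there. Here the protocol names the check, and its Data Availability section describes the article as the full protocol, so the point concerns what is stated.

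The protocol also nowhere says that agreement will be presented as proof; that reading comes from listing the comparison under robustness.

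**Conclusion.** The concern holds in a limited form. The planned comparison can reveal loss related to observed scores but cannot test departures from MAR. Under loss tied to unseen scores in the LLG, both analyses can be biased the same way, by similar though not necessarily equal amounts, and their agreement is not evidence of robustness.

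In the two-time-point illustrations with no true effect, the bias ranged from 0.17 to 0.34 SD. In the three-time-point case it was 0.20 to 0.33. These values depend on assumed mechanisms and on loss of about 31% overall, or about 40% in the LLG. The trial's 30% is an allowance, not an observed rate. If the mechanism is the same in both arms, or if loss depends only on arm, the contrast carries almost no bias. The documents do not show that informative loss will occur, only that the stated check could not tell. The sponsor should change the check, but the main analysis need not be replaced.

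**What to change.** Keep the complete-case comparison and label it descriptive. For the STROOP and WAFG primary outcomes, pre-specify one departure-from-MAR analysis:

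1. Shift the imputed values by arm over a stated range, towards slower responses for the LLG, and report the shift at which the hypothesis 1 and hypothesis 2 conclusions change.
2. As one fixed scenario, impute missing LLG values from the WLCG distribution given the observed scores.
3. Keep post scores in the imputation model for the 3-month outcome, so that loss following a poor observed gain stays within MAR.
4. Base the robustness statement on this analysis, read together with the reported withdrawal reasons.

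This needs no new data or visits. The shifts can be added to values already imputed. The control-based scenario needs further imputations under a second model, and its estimate is conservative, so it should be reported as a scenario and not as the main result.

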### Dissemination

Results will be disseminated regardless of the magnitude or direction of effects. They will be communicated to the scientific community through journal publications and congress presentations. We will also inform participants and interested individuals, groups, and institutions about trial results.

## Discussion

In this randomised controlled trial, we will investigate whether foreign language learning can improve EF in healthy older adults. The very few studies that have addressed this question to date yielded highly contradictory results. Consequently, well-controlled randomised trials are urgently needed in this field. In our study, we will compare changes in EF in healthy older adults after having attended an intensive three-week, face-to-face, group-based Spanish course for beginners (LLG) with a passive control group (WLCG). As primary outcomes, we will focus on two tasks requiring effortful attentional control, the STROOP, a measure of interference, and the WAFG, an assessment of divided attention. Our secondary outcomes will include tasks from the most widely accepted domains of EF – inhibition, shifting, and updating [30]. To extend the spectrum of EF covered and also to highlight the specificity of our results, we will include two additional domains that largely relate to linguistic [51] and attentional functions [52]. We will also investigate the longevity of any cognitive improvement after foreign language learning. Additionally, we will explore whether different levels of cognitive reserve and previous foreign language skills and usage influence our results.

Our study will have several strengths and limitations. One limitation is that the comparator is only a passive control condition. It is included to monitor improvements in cognitive performance through repeated measurements. The use of a passive control as the only comparison group has already been subject of extensive debate. Some authors argue that clinical trials should ideally include an active control of similar duration and intensity to control for effects attributable to specific treatment modalities, e.g. social activity [21, 64]. However, the inclusion of an active comparator depends on the research question. To date, foreign language learning has not provided clear evidence of maintaining or improving cognitive performance in older adults [21]. Thus, from an economic perspective, it is necessary to examine its effectiveness against a passive control before controlling for other influences or demonstrating its superiority over other activities [65]. Therefore, we decided not to include an active comparator. To still be able to differentiate effects of the intervention from more general effects, we included some secondary outcomes which should not benefit from foreign language learning. This can be presumed because verbal fluency and non-executive components of attention largely relate to cognitive functions which might be less affected by foreign language learning. Furthermore, a significant regression of previous foreign language skills and usage on our results could also be informative. Different levels of cognitive reserve have already been associated with changes in cognition after cognitive training [31]. Thus, assuming previous foreign language skills and usage are part of cognitive reserve, varying results depending on prior skills could indicate a direct effect of language training.

To our knowledge, we are conducting the first randomised controlled trial of its kind with a short and intensive foreign language training. We opted for this approach, as more intensive and short foreign language learning programmes were more likely to be associated with cognitive improvements than less intense trainings with longer durations [24–26, 28]. Furthermore, this short intervention period increases our chances of achieving the targeted sample size, since older adults, although retired, often lead an active lifestyle, and thus have limited time resources.

Our work might also contribute to the current debate on the bilingual advantage hypothesis. This hypothesis suggests that bilinguals perform better in cognitive domains involved in language control, particularly in EF, and suffer less cognitive decline compared to monolinguals [66]. However, accumulating evidence challenges this advantage. For example, a recent large-scale meta-analysis of 152 studies could not find any support for a bilingual advantage across all domains of EF after controlling for publication bias [67]. Although intensive foreign language training and bilingualism differ in important aspects (e.g. short-term learning vs. long-term use), we still might learn more about cognitive processes that underlie foreign language learning. This is of considerable importance as the bilingual advantage might only occur under certain circumstances, which are not yet fully understood [68]. Nevertheless, we would like to emphasise that this study was not intended to address the debate on the bilingual advantage. Our study concerns a well-defined pattern of foreign language usage and a low level of language skills. Thus, no general conclusion can be drawn about the bilingual advantage hypothesis, and any comparison with bilingualism should be taken with caution.

Preserving and enhancing cognitive health in older age is highly relevant, given our ageing world population [1]. As Bak [12] has already noted, if foreign language learning turns out to enhance EF in older adults, it might have clear-cut advantages over drugs or other provisions against cognitive decline. Foreign language learning is inexpensive, already widely available and easily combinable with other activities such as music or travelling. Therefore, foreign language learning could constitute an attractive and enjoyable opportunity to promote cognitive reserve, and thus healthy cognitive ageing.

